### Minimal residual disease detection

Upon obtaining the region-specific exome sequencing data, we integrated the data from each region to design a personalized MRD panel. Our surveillance strategy includes up to 150 somatic mutations identified in each patient, along with 21 well-established cancer-related driver mutations. In cases where a large number of somatic mutations are detected, we prioritize screening clonal mutations over subclonal mutations. To ensure the sensitive detection of low-frequency mutations, we employ ultra-deep sequencing at a depth of 100,000×, using a minimum input of 10 ng of circulating tumor DNA (ctDNA). ctDNA-based MRD is dynamically monitored to evaluate the clinical significance of ctDNA in plasma for detecting low levels of residual disease.

## Data analyses

### Multi-omics data integration

For the CLEVER cohort, we implemented a multidimensional profiling strategy encompassing three complementary analytical axes: molecular stratification (genomic whole-exome sequencing, transcriptomic RNA-seq, and proteomic GeoMx DSP protein), resolution scaling (bulk tissue analysis, single-cell resolution, and spatial mapping), and cross-platform integration. This framework was operationalized through molecularly barcoded aliquots derived from identical tumor regions, ensuring cellular and spatial concordance across omics layers.

#### WES + RNA-seq

Leveraging multi-region WES data, we reconstructed phylogenetic trees for each tumor to delineate evolutionary trajectory patterns within the Chinese lung cancer cohort, employing maximum parsimony-based phylogenetic reconstruction with bootstrap validation (*n* = 1000 replicates). Concurrently, we deconvolute immune cell composition, intercellular communication networks, and spatially resolved microenvironmental niches of different evolutionary trajectory patterns by integrating bulk RNA-seq, single-cell RNA-seq, and spatial transcriptomic profiles.

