## Study design and highlights

We conduct a prospective large-scale multi-region Chinese lung cancer cohort called CLEVER study from Peking University People’s Hospital. The cohort is divided into two subcohorts: the naïve cohort, which includes patients who have not received neoadjuvant therapy before surgery, and the neoadjuvant cohort, which includes those who have. During surgery, samples of tumor tissue, marginal tissue, and matched normal tissue are collected. These samples undergo comprehensive multidimensional omics analyses, including whole exome sequencing (WES), RNA sequencing (RNA-seq), single-cell sequencing, and multiple spatial omics techniques such as Stereo-seq, digital spatial profiling (DSP), and imaging mass cytometry (IMC). Additionally, preoperative blood samples are collected on the morning of the surgery, and postoperative blood samples are collected during a two-year follow-up period for longitudinal dynamic monitoring of minimal residual disease (MRD) (Figure 1A). The primary endpoint of the study are two-year disease-free survival (DFS) and overall survival (OS). The secondary endpoint is to identify available predictors of clinical benefit.

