### Sample collection

#### Tissue samples

In order to accurately sample and record the position, we have developed a standardized multi-region sampling process. Initially, the surgical sample is dissected along its maximum diameter. Equal-sized samples are then taken from one side of the tumor using a skin perforator. For smaller tumors, consider sampling from various locations on the opposite side. Samples from at least two tumor regions must be separated by 0.3 cm to 1 cm, depending on the tumor size, for inclusion in the study. Border samples should be collected at the interface between tumor and normal tissue to ensure that both tumor and normal samples are obtained. Paired normal tissue samples should be taken at least 2 cm away from the tumor edge. Last but not least, the central coordinates of each sampling point were recorded using a double-scale square and documented with photographs.

All tissue samples must be immediately placed into freezing tubes for preservation at -80°C. If the tumor is sufficiently large, a set of paraffin-embedded samples should also be collected for all tissues.

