### Whole exome sequencing and analysis

The DNA library is prepared with an input of 200 ng genomic DNA using the VAHTS Universal Plus DNA Library Prep Kit for Illumina V2. The subsequent hybridization capture is performed using the SureSelect XT target enrichment system. The final DNA library is quantified using the Qubit 3.0 and fragment detection is conducted with the Agilent 2100. Finally, the DNA library is sequenced using paired-end 150 bp reads on the Illumina NovaSeq 6000 platform.

The sequencing data is analyzed using the WES pipeline. The sequencing data from white cells is used to exclude germline mutations. Clean reads in FASTQ format are aligned to the human UCSC reference genome (hg19/GRCh37) using the Burrows-Wheeler Aligner (BWA, v0.7.15). Sambamba (v0.6.8) is used to process PCR duplicates in the mapped BAM files. The Genome Analysis Toolkit (GATK v4.0.11.0) is employed for local realignment and base quality recalibration to compute sequencing coverage and depth. Single nucleotide variations (SNVs) and small insertions and deletions (Indels: < 50 bp) are identified using GATK MuTect2 (v1.1.4). Multiple testing correction for gene-level mutation frequency comparisons will be performed using the Benjamini-Hochberg procedure, with an adjusted p-value (FDR) cutoff of < 0.05.

Based on multi-region sequencing, region-based tumor mutation calling is combined to recall tumor-informed mutations, allowing for the acquisition of new recalled mutations for each region. Using these recalled region-level mutations, the phylogenetic tree is reconstructed using the CNIPHER method,^[24]^ enabling the identification of clonal and subclonal mutations. Somatic copy number alterations (SCNAs) are processed using ASCAT (V2.3), which allows for the determination of intratumoral heterogeneity in both SNVs and SCNAs, specifically assessing subclonal mutation fractions and subclonal SCNAs fractions. This comprehensive analysis facilitates a deep understanding of evolutionary events within the tumor, characterized by intratumoral heterogeneity, clonal illusion, subclonal expansion, whole genome doubling, weighted genome integrity index (wGII), and loss of heterozygosity (LOH). These insights provide a detailed depiction of the tumor’s evolutionary landscape and its underlying genetic dynamics.

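### Two tree methods are named for the same multi-region exome data without saying which serves which purpose; separately, the bootstrap does not test branching in a two-region tumour if the leaves are the tumour regions plus a germline root

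*Protocol article*

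**What the plan says.** Three places in the protocol article bear on this point.

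- **Whole exome sequencing and analysis.** Mutations are recalled at region level across each tumour's samples, and from these "the phylogenetic tree is reconstructed using the CNIPHER method". The clonal and subclonal mutations are identified from that tree. On the reference sample: "The sequencing data from white cells is used to exclude germline mutations".
- **WES + RNA-seq**, under Multi-omics data integration. The purpose is given first: "we reconstructed phylogenetic trees for each tumor to delineate evolutionary trajectory patterns within the Chinese lung cancer cohort". The method named for these trees, which also start from the multi-region exome data, is described as "employing maximum parsimony-based phylogenetic reconstruction with bootstrap validation". The number of bootstrap resamples is set at 1000. The same section then describes the microenvironment by trajectory pattern. It gives no support level and does not say which samples are the leaves.
- **Tissue samples.** A condition for inclusion reads "Samples from at least two tumor regions must be separated by 0.3 cm to 1 cm", so two tumour regions are enough. Border and paired normal samples are collected as well.

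**The concern.** Two separate matters arise, and neither causes the other.

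**Method.** Both sections build a tree from the same kind of data, and neither mentions the other. A reader cannot tell whether the trajectory patterns come from the CNIPHER tree or the parsimony tree, or whether the clonal calls and the patterns come from the same tree. The clonal calls feed the subclonal fractions and set which mutations are preferred for the personalised MRD panel. The patterns define the groups whose microenvironment is described. If the two methods disagree for a tumour, its results depend on a choice that the text leaves open.

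**Bootstrap.** Calling the bootstrap a validation suggests that a poorly supported tree could be recognised as such. That requires at least two competing topologies. At the permitted minimum of two regions there may be only one, and such a tumour would then show full support with its branching untested. Small tumours are eligible: the inclusion criteria accept a short diameter of 15 mm, and the sampling section makes separate provision for smaller tumours.

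**Working it through.** The plan gives no computed figure to reproduce; the 1000 replicates are a setting. The check has four steps.

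**1. The method statements side by side**

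| | Whole exome sequencing and analysis | WES + RNA-seq |
|---|---|---|
| Data | region-level mutations from multi-region exome sequencing | multi-region exome data |
| Method | CNIPHER | maximum parsimony, 1000 bootstrap replicates |
| Stated use | clonal and subclonal mutations | evolutionary trajectory patterns |
| Link to the other tree | none | none |

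**2. Number of competing trees**

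Input from the protocol: at least two tumour regions. Assumption: the leaves are the tumour regions plus one germline root (white cells). For L leaves there are (2L − 5)!! unrooted binary topologies and L − 3 non-trivial splits that a bootstrap can test.

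| Tumour regions | L | Topologies | Testable splits |
|---|---|---|---|
| 2 | 3 | 1!! = 1 | 0 |
| 3 | 4 | 3!! = 3 | 1 |
| 4 | 5 | 5!! = 15 | 2 |
| 5 | 6 | 7!! = 105 | 3 |

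With two regions every replicate returns the only tree there is, so topology support is 100% for any data.

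This depends on the leaves. If the border sample is also a leaf, L = 2 + 1 + 1 = 4 and there are 3 topologies. Adding normal lung as well gives L = 5 and 15 topologies.

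**3. What the bootstrap still shows at two regions**

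Resampling mutations still varies branch lengths. With 200 mutations and a truncal fraction of 0.60 (both assumed), the bootstrap 95% range of that fraction is about 0.53 to 0.66. This measures how much is shared, not the order of branching.

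**4. What the bootstrap shows at three regions**

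Parsimony picks the grouping (two regions against the third) that most shared mutations support. With 200 mutations (assumed), of which 30 are informative, and 1000 replicates:

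| Informative mutations per grouping | Support for the three trees |
|---|---|
| 10 / 10 / 10 | 0.32 / 0.33 / 0.35 |
| 12 / 10 / 8 | 0.57 / 0.31 / 0.12 |
| 20 / 5 / 5 | 0.998 / 0.001 / 0.002 |

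The bootstrap therefore separates clear from unclear cases here.

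With no true branching order, so that each grouping is equally likely:

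- With 200 mutations and each grouping at probability 0.05, mean best support is 0.64. It reaches 0.70 in 33% of simulated tumours and 0.95 in 3%.
- With 5 to 50 informative mutations, best support reaches 0.70 in roughly 20–45% and 0.95 in about 2–5%. The range reflects the number of informative mutations and the handling of ties. Splitting a tied replicate between trees generally gives higher figures than counting it as unresolved.

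**The case against.** The strongest reply has five parts.

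- **The leaves are not defined.** Tumour, marginal and normal tissue are all collected and profiled. With a border leaf a two-region tumour has three topologies and the bootstrap is no longer trivial. This stands as a condition on the finding. It helps only in part: border samples are meant to contain both tumour and normal tissue, and the result is the weak three-topology case. A normal-lung leaf adds little, because a split of both tumour regions from normal and germline reflects truncal mutations and not branching between the regions.
- **The two methods may serve different trees**, for example one for clones and one for regions. That is possible, but the text does not say it. It is why this is an unreconciled statement and not a proven contradiction.
- **Two regions is a floor.** The share of tumours at that floor is not given and could be anything from none to all. This stands.
- **Trajectory patterns are not defined by branching order.** The exome section describes evolution through subclonal fractions, genome doubling, wGII and LOH. This limits the harm, but the patterns are still said to be drawn from the trees.
- **A support level is often left to an analysis plan.** Agreed: its absence alone would be no finding. It matters here only because the article presents the bootstrap as validation and admits tumours for which no level can discriminate.

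A reader might infer that the bootstrap can never fail, so that patterns count as validated whatever the data show. The documents do not support that. From three regions support can be low, and nowhere does the article say that patterns are accepted regardless of support. Nor does the protocol concede a flaw; it only permits two-region tumours.

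**Conclusion.** The point holds in a limited form.

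1. The exome and integration sections name different tree methods for the same data and do not say which tree gives the clonal calls and which gives the trajectory patterns. This follows from the text and needs no assumption.
2. For a two-region tumour with only the tumour regions and a germline root as leaves, topology support is 100% by construction (1 topology, 0 testable splits), so branching is not tested. Branch lengths and truncal fraction are still informed.
3. From three regions the test is real but weak at lenient thresholds. With no branching signal, about 20–45% of simulated tumours pass 70% support and about 2–5% pass 95%. These figures rest on simulated mutation counts and tie rules, not on trial data.

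The reach cannot be sized, because the share of two-region tumours is unknown. The primary DFS and OS endpoints and the sample size do not depend on this point. What is affected is the evolutionary description, which is a central aim of the study.

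**What to change.** - Reconcile the two sections. State which tree is primary for the clonal and subclonal calls and which for the trajectory patterns, and make the other method a sensitivity analysis. Which method takes which role is the investigators' choice.
- State which samples are leaves, including whether border and normal samples are.
- Claim bootstrap-supported branching only for trees with at least four leaves, for example three tumour regions plus root, and at a support level fixed in advance. The simulation argues for a strict level, but the documents do not dictate one. A normal-lung sample should not be used to make up the fourth leaf, for the reason given above.
- Report two-region tumours as *branching order not assessable* and keep them in the clonal and subclonal analyses.

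The cost is a change of wording and analysis rules, with no new samples or assays. The drawback is that fewer tumours contribute to the branching-pattern comparison. The number of tumours with two regions should be reported so that readers can see how many.

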#### ScRNA-seq + Spatial Transcriptomics

At present, there are two main methods for integrating scRNA-seq and spatial transcriptome data: Deconvolution and Mapping. Deconvolution aims to separate discrete cell subpopulations from the mixture of mRNA transcripts at each capture point based on single-cell data. The GeoMx DSP hybrid gene expression data based on ROIs can construct cell type-specific gene expression characteristics using single-cell data through the SPOTlight,^[29]^ and then use the regression model to infer the proportion of each cell type in the GeoMx ROI. Mapping can locate the specified cell subtypes based on scRNA onto spatial sections and lock onto specific ecological niches of tissues. We use Seurat v4 anchors to map single-cell clusters onto spatial coordinates, estimating cell-type proportions at each spot and ROI. This leverages canonical correlation analysis (CCA) to align modalities and transfers cell-type labels from scRNA-seq to Stereo-seq.

#### IMC + Spatial Transcriptomics

After cell segmentation and clustering in IMC images, we co-register IMC cell neighborhoods with spatial transcriptomics coordinates through image registration algorithms and probabilistic coordinate mapping. This enables precise superimposition of protein expression-defined tissue microenvironments onto transcriptomically annotated cellular architectures. For cross-modal feature integration, we implement graph neural network architectures^[30]^ (Graph Convolutional Networks or Graph Attention Networks) that jointly learn from protein expression gradients and transcriptomic profiles within spatially constrained cellular graphs. If protein and gene expression share common underlying factors (such as cell type or functional status), we can also make inferences through probabilistic models (such as Bayesian factor analysis).

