### Spatial enhanced resolution omics-sequencing (stereo-seq)

The tissue was embedded in an OCT embedding agent (Sakura, 4583) and stored at -80°C. It was then sectioned into 10 μm thick slices using a cryotome (Leica, CM1950). Tissue structure was identified through H & E staining. Appropriately sized sections were placed on the Stereo-seq chip, and tissue integrity was assessed using ssDNA staining (Invitrogen, Q10212). Following the manufacturer’s protocol, chip permeation, RNA capture, reverse transcription, and cDNA library construction were completed.

Spatial transcriptome data were processed using Spaceranger (v.1.2.2). To achieve spatial localization of cell subsets on the spatial transcriptomics (ST) slides, we integrated the Stereo-seq data with single-cell RNA sequencing (scRNA-seq) data using the Seurat package. Seurat estimated the expression abundance of each cell subset at each spatial location by analyzing the similarity of expression patterns, thereby mapping the complete spatial distribution of cell types. These results are suitable for downstream analysis.

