### Imaging mass cytometry

The paraffin-embedded tissues were sectioned into 4 μm slices and heated at 68°C for 1 h. The slices underwent dewaxing twice in xylene, followed by rehydration through a graded series of ethanol solutions at concentrations of 95%, 85%, and 75%. Antigen retrieval was conducted by heating the slices at 100°C for 30 min, followed by natural cooling. Subsequently, the slices were washed twice with PBS-TB for 5 min each and then blocked with SuperBlock for 30 min. After blocking, the slices were washed three additional times with PBS-TB and incubated overnight at 4°C with a metal-labeled antibody cocktail (Maxpar® X8 Kit). Post-incubation, the slices were washed and treated with 1.25 μmol/L Intercalator-Ir in PBS-TB at room temperature for 30 min, followed by washes with PBS-TB and distilled water. The prepared sections were then scanned using a Hyperion Imaging System to generate multiple images.

The IMC data processing involved four steps: overflow compensation, image denoising, contrast enhancement, and cell segmentation. The range of label expression was normalized to the 99th percentile for each channel, and batch effects were corrected using Harmony (v0.1.0). Clustering of cells was performed using Rphenograph (v0.99.1) with 100 nearest neighbors, and the cluster means were visualized as an annotated heat map.^[27]^ The K-means clustering method with (k = 15) was employed to identify cell neighborhoods (CNs) using a clustering window of the 20 nearest cells, based on Euclidean distance. Cell-cell interactions were analyzed using an arrangement assay facilitated by the imcRtools package (v1.0.2).^[28]^

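### The planned image co-registration of IMC with spatial transcriptomics cannot deliver the near-cellular overlay claimed: Stereo-seq is on frozen tissue and IMC on a separate paraffin set, and GeoMx, which shares the paraffin format, is resolved only to ROI level

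*Protocol article*

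**What the plan says.** Five places in the protocol article bear on this.

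- **IMC + Spatial Transcriptomics.** After segmentation and clustering of the IMC images, "we co-register IMC cell neighborhoods with spatial transcriptomics coordinates through image registration algorithms and probabilistic coordinate mapping". The stated result: "This enables precise superimposition of protein expression-defined tissue microenvironments onto transcriptomically annotated cellular architectures". Graph neural networks then "jointly learn from protein expression gradients and transcriptomic profiles within spatially constrained cellular graphs". A probabilistic factor model is offered as an alternative. The spatial transcriptomics platform is not named.
- **Stereo-seq.** "The tissue was embedded in an OCT embedding agent (Sakura, 4583) and stored at -80°C", then cut at 10 μm on a cryotome.
- **Imaging mass cytometry.** "The paraffin-embedded tissues were sectioned into" 4 μm slices. Cell neighborhoods are found by K-means over windows of the 20 nearest cells.
- **Tissue samples.** "All tissue samples must be immediately placed into freezing tubes for preservation at -80°C". Paraffin comes in addition: "If the tumor is sufficiently large, a set of paraffin-embedded samples should also be collected for all tissues".
- **Multi-omics data integration.** Aliquots are taken from the same tumor regions, which is described as "ensuring cellular and spatial concordance across omics layers".

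A second spatial platform, GeoMx DSP, is run on FFPE sections. The subsection on single-cell and spatial transcriptomics treats its output as mixed expression per ROI, from which cell-type proportions are inferred.

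**The concern.** Image registration needs something common to both images: the same section, or neighboring sections of one block in which the same structures can be followed. The article describes no such link between IMC and Stereo-seq, and the tissue formats it gives rule out a shared block. A registration algorithm will still return a transform. Protein and RNA features joined through that transform would come from different tissue, yet would be read as measured spatial co-localisation. A graph network trained on them would take the joint structure at face value. Microenvironment niches, and any marker derived from them, would then carry a spatial precision that the sampling does not provide.

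**Working it through.** No arithmetic applies, and the plan gives no figure to reproduce. The check is a comparison of tissue format, sample origin and resolution for each platform that could be the partner of IMC.

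| | IMC | Stereo-seq | GeoMx DSP |
|---|---|---|---|
| Tissue | Paraffin | OCT-embedded, frozen | FFPE |
| Section thickness | 4 μm | 10 μm | not stated |
| Sample set (Tissue samples section) | additional set, large tumors only | default frozen set | additional set, large tumors only (inferred from FFPE format) |
| Unit of spatial data | cells; neighborhoods of 20 nearest cells | capture spots with cell labels transferred from scRNA-seq | ROI mixtures, deconvolved to cell-type proportions |
| Could share a block with IMC? | – | no | yes |
| Could support an overlay at cellular scale? | – | no, no common tissue plane | no, ROI resolution only |

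**Step 1, IMC and Stereo-seq.** The default is to freeze every sample. Paraffin is collected on top of that, subject to tumor size. A piece embedded in OCT and frozen is not the piece embedded in paraffin. Even if one core were split in two, the halves are processed and cut as separate blocks, and the article describes no serial-section pairing across them. The two images have no tissue plane in common.

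**Step 2, scale.** The IMC unit to be placed is a neighborhood of about 20 cells, which is small against the piece of tissue it sits in. Mapping neighborhoods probabilistically, rather than single cells, does not solve the problem: with no shared plane, nothing at that scale anchors the map. What the two data sets can share is membership of the same tumor region.

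**Step 3, IMC and GeoMx.** Both use paraffin, so sections of one block could be registered. The transcript side is then a mixture per ROI. That supports a comparison of IMC composition with GeoMx composition within the same ROI, but not an overlay on transcriptomically annotated cells.

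**Step 4, which platform is meant.** The subsection says only spatial transcriptomics. The Stereo-seq section uses that term for its own slides, and the subsection on single-cell and spatial transcriptomics transfers cell labels to Stereo-seq, which fits the description of annotated cellular structure. GeoMx is also discussed under the spatial transcriptomics heading. The text allows either reading, and neither supports the stated precision.

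**Step 5, reach.** The COCA step works with samples as rows and cluster membership per platform, so it needs no spatial pairing. The recurrence model takes summary metrics from the integration section; the article does not say whether features from fused IMC data are among them.

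**The case against.** **No one-to-one matching is stated.** A reader might infer that individual cells are to be paired across platforms. The article does not say so: it speaks of neighborhoods, microenvironments and probabilistic mapping. That stands, and the point does not depend on cell pairing. Claims of precision, cellular graphs and cellular concordance still imply a scale close to the cell, and Step 2 shows that the neighborhood scale fails as well.

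**The platform may be GeoMx.** This is a fair reading, and registering IMC to GeoMx on one paraffin block would be compatible with the text. It rescues the registration but not the claimed resolution.

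**A distance between mismatched tissue.** It is tempting to take the 0.3 to 1 cm in the sampling section and convert it into a displacement between the frozen and paraffin material. That figure is the required separation between tumor regions. The article gives no distance between the two formats within a region, so no numerical displacement can be supported.

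**Section pairing is laboratory detail.** Which block and which serial section are used may well be in the full protocol, and their absence from an article is not a fault. The criticism rests on what is stated: two incompatible formats, and an explicit claim of precise overlay and cellular concordance.

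**The step is exploratory.** This stands. A reader might infer that the primary results or the recurrence model are compromised; the article shows no such effect.

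**Conclusion.** For IMC with Stereo-seq, the claimed overlay and the claim of cellular concordance across layers are not supported by the sampling described; the two data sets can be matched at tumor-region level at best. For IMC with GeoMx, registration is feasible where paraffin exists, at ROI level only. The conclusion assumes that the tissue formats in the article are those actually used and that no unreported shared-block design links the frozen and paraffin material. There is no numerical size to give. The consequence is limited to exploratory protein-RNA microenvironment findings and any biomarkers drawn from them. The two-year DFS and OS endpoints, the sample size and the COCA clustering are not affected. The change is worth making because it is cheap and prevents false co-localisation results.

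**What to change.** 1. In the IMC + Spatial Transcriptomics subsection, name the platform to which IMC is registered.
2. Restrict image co-registration to IMC and GeoMx sections of the same paraffin block, where available, and analyse the joint data at ROI level.
3. Link IMC to Stereo-seq only through region-level summaries, such as cell-type proportions and niche composition per tumor region.
4. Run the graph network within one platform's own coordinates, or on region summaries.
5. Replace the claim of precise overlay in that subsection, and the word cellular in the concordance claim under Multi-omics data integration, with wording at region or ROI level.

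The cost is mainly plan wording, plus laboratory attention to which paraffin sections go to IMC and GeoMx. IMC-GeoMx registration would be available only for tumors large enough to yield paraffin samples. The scientific price is giving up a near-cellular protein-RNA claim that the described sampling cannot support.
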